### Secondary outcome analysis of the trial

To formally compare sub-groups, two predefined individual level variables (with interaction term) will be added one at a time, namely gender and ethnicity a p value of 0.01 will be used to take into account multiple testing. These will answer plausible questions, i.e. that the effect of the intervention differs by gender or by ethnicity. Unadjusted analyses originally performed in MLwiN will be repeated in Stata 10[39] using fixed effect Sandwich estimates to take account of the cluster randomisation to assess robustness of conclusions. These are exploratory analyses that are hypothesis generating.

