## Methodology

### Sampling and recruitment of schools

#### Trial 1 – intensive vs. Less intensive intervention

The RHS plan to establish their Campaign for School Gardening to schools in the London region in the autumn of 2009. The RHS Campaign provides intensive support in each region to 10 schools through support from an RHS School Gardening Regional Advisor (the intensive intervention). The remaining schools will have access to support through twilight training sessions for staff and other activities (the less intensive intervention).

Twenty-six schools will be recruited from four boroughs in London: Wandsworth; Tower Hamlets; Greenwich; and Sutton. Of the 26 schools we will randomly allocate 10 schools to receive the intensive intervention and 16 schools to receive the less intensive intervention. The allocation sequence will be generated by the trial statistician. All schools will be allocated at the same time. Time between notification of allocation and the start of the intervention will be as short as possible. It will not be possible to randomise schools to receive no intervention at all since the RHS is committed to providing support to all schools who register an interest in the Campaign. As a consequence of this, we will recruit a second set of schools into a linked trial.

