#### Trial 2 – less intensive vs. Delayed intervention

Following selection of schools into trial 1, we will contact schools from neighbouring boroughs in London: Lewisham; Lambeth; Merton and Newham. We anticipate that these boroughs will have approximately 130 primary schools. We will aim to recruit 32 schools into the second trial. Of these schools, 16 will be randomly allocated to sign up to the RHS Campaign for School Gardening and to receive the less intensive intervention and 16 schools will act as comparison schools. The schools will be randomly allocated to the associate (i.e. less intensive) intervention or the comparison group. The comparison schools will have no active RHS intervention during the trial. They will be offered delayed access to the less intensive intervention at the end of the study.

It will not be possible to blind schools to their intervention group because of the nature of the intervention. The fieldworkers will be blinded to the allocation of schools to the intervention (more or less intensive) and comparison arms of the study.

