### Proposed outcome measures

#### The primary outcome measure will be the following

· Food:

· Daily portions of fruit and vegetable intake at follow-up (15 months after baseline)

· Daily portions of fruit intake

· Daily portions of vegetable intake

The effectiveness of either intervention would be determined by an increase in mean intake in one of the following: mean intake of fruit, mean intake of vegetables, or mean intake of fruit and vegetables at follow-up after adjusting for baseline

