### Primary analyses

A random or fixed intercepts model of primary and secondary outcomes will be used allowing for hierarchical structure of data caused by cluster randomisation: child within class within school. MLwiN [47] will be used for this analysis. The single covariate for the intervention group will be included in the model (treated as a random effect since schools in the trial are themselves a random sample from the population of schools).

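### The robustness check repeats only unadjusted analyses, so it misses the baseline-adjusted estimate that decides effectiveness, and its sandwich variance is mildly too small with 26 or 32 schools

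*Protocol article*

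**What the plan says.** Under Secondary outcome analysis of the trial, the protocol article plans a second run, in Stata, of those MLwiN analyses that are unadjusted. The method and purpose of this rerun are given as "using fixed effect Sandwich estimates to take account of the cluster randomisation to assess robustness of conclusions". The next sentence reads "These are exploratory analyses that are hypothesis generating".

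The effectiveness criterion appears under Research questions and again under Proposed outcome measures. It is an increase in mean fruit, mean vegetable, or "mean intake of fruit and vegetables at follow-up after adjusting for baseline".

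Under Primary analyses, a multilevel model "will be used allowing for hierarchical structure of data caused by cluster randomisation", and "The single covariate for the intervention group will be included in the model". No baseline term is mentioned there.

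The clusters are schools. In Trial 1, "we will randomly allocate 10 schools to receive the intensive intervention and 16 schools to receive the less intensive intervention". For Trial 2, "We will aim to recruit 32 schools into the second trial", split 16 and 16. The Multiple comparisons section sets a 1% level for all tests.

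**The concern.** There are two separate questions.

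The first is scope. The check is given the job of assessing whether the conclusions are robust. The conclusion about effectiveness rests on a baseline-adjusted difference, and the check is confined to unadjusted analyses. If the two estimates differ, for instance because baseline intake is imbalanced between arms with so few schools, the check says nothing direct about the result being reported.

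The second is method. A cluster-robust variance is justified by a large number of clusters. With 26 or 32 schools it is too small on average, more so when the arms are unequal (as in Trial 1) or school sizes vary. The relative effect is larger at the 1% level, which is the level the article sets. A check that is itself somewhat liberal gives less reassurance than it appears to.

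**Working it through.** The article gives no figure for the accuracy of the check, so there is none to reproduce.

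**Scope.** Side by side: the decision uses follow-up intake after adjusting for baseline; the check uses unadjusted analyses; the primary model as described has the intervention group as its single covariate. As written, the check repeats that single-covariate model and does not reach the adjusted estimate. No arithmetic is needed.

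**Method: inputs.** From the article: 10 v 16 and 16 v 16 schools; ICC 0.125 (vegetables); 50 children per school and 75% follow-up, so 0.75 × 50 = 37.5, about 38 per school. Assumed: coefficient of variation (CV) of school size from 0 to 0.5, normal data, class level ignored.

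**Method: closed form for equal school sizes.** With g1 and g2 schools per arm and school-mean variance s²:

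- true variance of the difference = s²(1/g1 + 1/g2)
- expected uncorrected sandwich variance = s²[(g1-1)/g1² + (g2-1)/g2²]

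Trial 1: (9/100 + 15/256)/(1/10 + 1/16) = 0.1486/0.1625 = 0.914. Multiplying by G/(G-1) = 26/25 gives 0.951.

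Trial 2: (15/256 + 15/256)/(1/16 + 1/16) = 0.1172/0.125 = 0.9375. Multiplying by 32/31 gives 0.968.

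On the standard-error scale (square roots) these are 0.956 and 0.975 in Trial 1, and 0.968 and 0.984 in Trial 2.

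For Trial 2 with equal school sizes the error rate follows exactly, because the sandwich variance is then 0.9375 times the pooled t-test variance on 30 df:

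- uncorrected, normal reference, 5%: 2P(t30 > 1.960 × 0.968) = 2P(t30 > 1.898) = 6.7%
- uncorrected, normal reference, 1%: 2P(t30 > 2.576 × 0.968) = 2P(t30 > 2.494) = 1.8%
- corrected, t on 31 df, 5%: 2P(t30 > 2.040 × 0.984) = 2P(t30 > 2.006) = 5.4%
- corrected, t on 31 df, 1%: 2P(t30 > 2.744 × 0.984) = 2P(t30 > 2.699) = 1.1%

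**Method: simulation under no effect**, needed for unequal arms and unequal school sizes. Ranges are over CV 0 to 0.5.

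| Test | Trial 1, nominal 5% | Trial 1, nominal 1% | Trial 2, nominal 5% | Trial 2, nominal 1% |
|---|---|---|---|---|
| Sandwich, uncorrected, normal reference | about 7-9% | about 2-3% | 6.7-7.8% | 1.7-2.4% |
| Sandwich, G/(G-1) factor, t(G-1) | 5.6-7% | 1.3-1.8% | 5.3-6.4% | 1.1-1.5% |
| t-test on school means, G-2 df | 4.8-5.1% | 0.9-1.1% | 4.8-5.1% | 0.9-1.1% |

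The low ends of the Trial 2 sandwich rows agree with the closed form. The high ends come from strongly unequal school sizes.

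**The case against.** The strongest reply is that the article fixes neither an uncorrected variance nor a normal reference. Those details are commonly left to an analysis plan, and with the simple correction the inflation is modest. This stands, and it is why the size is given for both variants and the milder one comes first.

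It is also fair that the analyses are labelled exploratory and that no effectiveness decision is assigned to them. That stands too, although the same text gives the check the task of assessing the robustness of conclusions.

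A third reply is that the scope problem starts in Primary analyses, whose single-covariate model is itself unadjusted, so the check merely follows it. This explains the gap without closing it: the criterion for effectiveness is still the adjusted difference.

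A reader might infer three stronger points that the article does not support:

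- That being unadjusted makes the check understate uncertainty. Leaving out baseline normally widens the standard error. Scope and variance bias are separate matters.
- That the primary model shares the weakness because it is fitted by maximum likelihood and tested against the normal distribution. The article does not state the estimation method or the reference distribution.
- That the check will tend to confirm a false positive. Even if a maximum-likelihood normal test is assumed for the primary analysis, the corrected sandwich agreed with its false positives in 66-81% of simulated cases at 5% and 50-66% at 1%. Near-automatic agreement (up to 99.6% at 5%) arose only with the uncorrected form and near-equal school sizes.

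**Conclusion.** The concern holds in a limited form. The mismatch of scope follows from the text alone and needs no assumption: the stated check does not test the estimate on which effectiveness is judged. The variance point is real but modest. At the 1% level the true error is about 1.1 to 1.8 times nominal with the simple correction, and about 1.7 to 3 times without it; Trial 1 is worse because of its 10 v 16 split. These sizes depend on the assumed spread of school sizes, the assumed form of the sandwich and the article's ICC of 0.125. They describe a weak check and do not show that the primary decision is wrong.

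**What to change.** In Secondary outcome analysis of the trial:

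- Apply the check to the same baseline-adjusted estimate that decides effectiveness. State under Primary analyses whether baseline is in the model, so that the decision, the model and the check refer to one estimate.
- Replace the plain sandwich with a t-test on baseline-adjusted school means, on schools minus 2 degrees of freedom (24 in Trial 1, 30 in Trial 2, fewer if school-level terms are added), or with a bias-reduced cluster-robust variance (CR2) and Satterthwaite degrees of freedom.

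The cost is wording and a few lines of code, with no change to design or data collection. Intervals become slightly wider. With equal school sizes, the school-mean t interval compared with the corrected sandwich is 2.064/(2.060 × 0.975) = 1.03 times as wide in Trial 1 and 2.042/(2.040 × 0.984) = 1.02 times in Trial 2. Compared with the uncorrected normal version it is 2.064/(1.960 × 0.956) = 1.10 and 2.042/(1.960 × 0.968) = 1.08 times.

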### Multiple comparisons

No adjustment will be made for multiple comparisons of these pre-specified secondary analyses. All tests will use a 1% significance level, and report 95% confidence intervals.

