### Proposed sample size

Cluster randomisation will be used, randomising at the school level, because the intervention will involve whole schools and participating classes. Based on results from our previous work on schools in a national sample, we estimate the standard deviation for the amount of vegetables eaten to be 85 g and for fruit 143 g. The associated intraclass correlation coefficient for total vegetables from Project Tomato was 12.5% and for fruit 11.4% (unpublished results). This sample of 50 children (one year 3 class and one year 4 class) from each school, will give a design effect of approximately 6.6 for vegetables and 7.1 for fruit to take account of the cluster randomisation. To have 90% power to detect a 0.5 portion difference in vegetable intake, 627 per group are required, i.e. about 13 schools using 2 classes from each school. To have 90% power to detect a 1 portion difference in fruit intake, 482 per group are required, i.e. about 10 schools. Based on results from our evaluation of the School Fruit and Vegetable Scheme, 75% who completed the Child And Diet Evaluation Tool (CADET) at baseline also completed the final follow up CADET. To allow for this margin of safety, 16 schools per group will be selected in each group apart from the intensive intervention group where it is only possible for 10 schools to be involved. The size of effect the study is powered to detect, (one half of a portion of vegetables or one portion of fruit) was chosen because it was considered the smallest improvement in intake that was worthwhile detecting with the achievable sample size, and considering the nature of the intervention.

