### Subgroup analyses

The subgroup analyses outlined below will be investigated in an exploratory manner using the same modelling procedure as above. These will be tested at the 1% significance level.

· Differences between boys and girls

· Differences between school year groups

· Differences between quintiles of Index of Multiple Deprivation Scores

· Efficacy subset analysis

· Whilst it is often argued that the most meaningful results are based on Intention-to-Treat (ITT) principles, for intervention analysis such as this study, the degree to which schools participate in the intervention is vital to the main outcome. It would therefore be illuminating to compare the results from ITT and efficacy subset analysis to examine the differences in effect size generated [48].

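### The only significance level in the protocol is 1%, worded for all tests, but the sample size matches two-sided 5% (80 g portion assumed); read literally, the stated numbers give about 75% power, not 90%

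*Protocol article*

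**What the plan says.** Three sections of the protocol article give a test level, and each gives 1%.

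- Secondary outcome analysis of the trial, on the gender and ethnicity interactions: "a p value of 0.01 will be used to take into account multiple testing".
- Multiple comparisons: "No adjustment will be made for multiple comparisons of these pre-specified secondary analyses", followed at once by "All tests will use a 1% significance level, and report 95% confidence intervals".
- Subgroup analyses: "These will be tested at the 1% significance level".

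The Primary analyses section names no level. Proposed sample size states neither a level nor whether the test is one- or two-sided. It says "To have 90% power to detect a 0.5 portion difference in vegetable intake, 627 per group are required" and "To have 90% power to detect a 1 portion difference in fruit intake, 482 per group are required". Its other inputs are the standard deviations ("we estimate the standard deviation for the amount of vegetables eaten to be 85 g and for fruit 143 g"), intraclass correlations of 12.5% and 11.4%, 50 children per school, design effects of 6.6 and 7.1, and 75% completion at follow-up. The target effect is given in portions ("one half of a portion of vegetables or one portion of fruit"), with no weight in grams.

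**The concern.** The sentence on the 1% level speaks of all tests and exempts none. Taken literally it sets the threshold for the three primary intake outcomes in each trial. A sample size worked out at 5% then no longer delivers its stated power.

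The sentence also pairs a 1% test with a 95% interval. Any result with p between 0.01 and 0.05 would have an interval that excludes zero beside a test called non-significant, and the text does not say which of the two a reader should follow.

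At stake is the success threshold. With p = 0.03 on vegetables, the document supports one answer if the sentence is read literally and another if the level implied by the sample size is used. That choice should not be open once outcome data are seen.

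**Working it through.** **Inputs from Proposed sample size.** SD 85 g (vegetables) and 143 g (fruit); ICC 0.125 and 0.114; 50 children per school; stated design effects 6.6 and 7.1; 75% completion, so 0.75 × 50 = 37.5 completers per school; 16 against 16 schools in Trial 2 and 10 against 16 in Trial 1. **Assumed:** a portion of 80 g, so the differences are 40 g (vegetables) and 80 g (fruit).

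**1. Reproducing the stated figures.** n per group = 2 × SD² × (z_α + z_β)² / δ², rounded up, times the stated design effect, with z_β = 1.2816.

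- Two-sided 5% (z = 1.960), vegetables: 2 × 85² × 3.2415² / 40² = 94.9, so 95; 95 × 6.6 = 627.0 (stated 627).
- Two-sided 5%, fruit: 2 × 143² × 3.2415² / 80² = 67.1, so 68; 68 × 7.1 = 482.8 (stated 482).
- Two-sided 1% (z = 2.5758), vegetables: 134.4, so 135; 135 × 6.6 = 891, about 18 schools.
- Two-sided 1%, fruit: 95.1, so 96; 96 × 7.1 = 682, about 14 schools.
- At 80 g, one-sided 5% gives 515 and 391, and one-sided 1% gives 779 and 596. Neither fits.

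**2. How far this depends on the portion weight.** Only the ratio (z_α + z_β)/δ enters the formula, so another level can be matched by another weight.

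| Portion | Two-sided 5% (veg, fruit) | Two-sided 1% (veg, fruit) |
|---|---|---|
| 70 g | 818, 625 | 1162, 888 |
| 80 g | 627, 483 | 891, 682 |
| 90 g | 495, 383 | 706, 540 |
| 95 g | 449, 341 | 634, 483 |
| 100 g | 403, 305 | 574, 433 |

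Two-sided 1% fits only near 80 × (2.5758 + 1.2816)/(1.960 + 1.2816) = 95.2 g. One-sided 1% comes within 3% at 90 g (614 and 469). The round value that reproduces both figures is 80 g at two-sided 5%, but the document does not confirm that weight.

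**3. Power of the stated numbers at two-sided 1% (80 g).** Vegetables: 627/6.6 = 95 effective children per group; 40 / (85 × √(2/95)) = 3.243; Φ(3.243 − 2.576) = 74.8%. Fruit: 482/7.1 = 67.9; 80 / (143 × √(2/67.9)) = 3.259; Φ(3.259 − 2.576) = 75.3%.

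**4. Power of the schools planned.** Design effect = 1 + 36.5 × ICC, which is 5.5625 for vegetables and 5.161 for fruit. SE = SD × √[design effect × (1/(37.5k₁) + 1/(37.5k₂))]. Power is Φ(δ/SE − z) by the normal approximation, or from the non-central t with 30 df (Trial 2) and 24 df (Trial 1).

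| Trial, outcome | SE (g) | δ/SE | 5%: normal / t | 1%: normal / t |
|---|---|---|---|---|
| Trial 2 vegetables | 11.57 | 3.456 | 93% / 92% | 81% / 75% |
| Trial 1 vegetables | 13.20 | 3.031 | 86% / 83% | 68% / 60% |
| Trial 2 fruit | 18.76 | 4.265 | 99% / 98% | 95% / 93% |
| Trial 1 fruit | 21.39 | 3.741 | 96% / 95% | 88% / 82% |

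These figures take no credit for baseline adjustment, because the document gives no baseline–follow-up correlation.

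**5. A separate matter that affects the comparison.** From the stated ICCs, 1 + 49 × 0.125 = 7.1 belongs to vegetables and 1 + 49 × 0.114 = 6.6 to fruit, so the printed design effects look exchanged. The cost of moving from 5% to 1% must therefore be read at one design effect: 627 to 891 for vegetables at the stated 6.6.

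**The case against.** The strongest reply is about scope. The 1% sentence follows one on pre-specified secondary analyses and stands between a section that calls its analyses exploratory and the subgroup section. It can be read as covering only those tests. A sample size that fits 5% and the choice of 95% intervals both favour that reading, and a condensed article may leave the primary level to a fuller plan. This stands. A reader might infer that the primary outcomes are certainly tested at 1% and that 90% power is certainly not delivered; the text does not establish that. What survives is that the sentence says all tests and that the only level given does not fit the sample size at the assumed portion weight.

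Four further points limit the size of the problem.

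- The loss is not general. Trial 2 fruit stays above 90% at 1% with the design effect taken from the ICC. It drops to 86% only if 7.1, which belongs to 50 children per school, is kept after a quarter of them are lost.
- Trial 1 vegetables fall short of 90% even at 5% (86%), because of the 10-school arm, a limit the protocol itself states. The 1% level deepens that gap but does not create it.
- The primary comparison adjusts for baseline. If the correlation were 0.3 to 0.5 (an assumption) and the variance fell by the factor 1 − r², Trial 2 vegetables at 1% would rise from 81% to between 85% and 92%. Trial 1 vegetables would stay below 90%, at 73% to 82%.
- A portion near 95 g would reconcile the sample size with two-sided 1%. The document neither states nor excludes it.

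The interval mismatch and the statement that no adjustment is made, beside a stricter level adopted for multiple testing, are matters of reporting and wording. A 95% interval can properly serve estimation. They do not show an invalid analysis.

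**Conclusion.** The concern holds as a conflict between a literal rule and a stated power. With 80 g portions, the planned numbers match two-sided 5%. At 1% the stated 627 and 482 per group give about 75% power. For the schools actually planned, vegetables fall below 90% in both trials, Trial 1 fruit falls slightly below, and Trial 2 fruit does not.

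This rests on three things: a portion weight the document does not give, a reading of the 1% sentence that includes the primary outcomes, and no credit for baseline adjustment. If the sentence is meant for secondary analyses only, alpha causes no power conflict and the defect is its unrestricted wording.

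**What to change.** 1. In Proposed sample size, state the two-sided 5% level on which the figures appear to rest, and the portion weight in grams.
2. In Multiple comparisons, limit the 1% sentence to secondary and subgroup tests. If 1% is meant for the primary outcomes, restate the power of each trial at that level.
3. Either match the confidence level to the test level, or say that the 95% intervals are for estimation and do not decide significance.

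The first option under item 2 costs a few words in two sections and no extra schools. Keeping 1% for the primary outcomes makes the stated power less favourable, and restoring 90% for vegetables would take about 18 schools per group instead of 13 at the stated design effect. A 5% familywise rule across the three primary intake outcomes would be a different change: the sample size does not assume it, and it would itself cost power. The level should be settled before outcome data are seen.

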### Subgroup analyses

The subgroup analyses outlined below will be investigated in an exploratory manner using the same modelling procedure as above. These will be tested at the 1% significance level.

· Differences between boys and girls

· Differences between school year groups

· Differences between quintiles of Index of Multiple Deprivation Scores

· Efficacy subset analysis

· Whilst it is often argued that the most meaningful results are based on Intention-to-Treat (ITT) principles, for intervention analysis such as this study, the degree to which schools participate in the intervention is vital to the main outcome. It would therefore be illuminating to compare the results from ITT and efficacy subset analysis to examine the differences in effect size generated [48].

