### Discontinuation criteria

Analysis will follow the principle of intention-to-treat as far as possible. We will therefore include in analyses all schools and children initially randomised, including them for analysis purposes in the intervention group originally allocated to them. To this end, all reasonable and ethical steps will be taken to ensure completeness of follow-up of outcome measures.

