### Process measures

Process evaluations are useful to identify adherence level to the intervention for each school. At baseline and follow-up, schools will be asked a set of gardening questions which are based on the RHS school bench marking system that ranks schools on their gardening activity levels from 1–5. An email consisting of different questions about gardening activities within the school, will be sent to the class teacher to capture what fruit and vegetables each school grows and harvests. This information will be captured via email in October 2010 for trial year one and October 2011 for trial year two. For the intense intervention trial schools in trial one, additional details regarding the intervention activities within each school will be captured by the regional advisor. For the less intense intervention, level of involvement in the twilight sessions for both trials one and two will be recorded. The regional advisor will keep a record of teacher’s attendance. The nature of this type of intervention allows schools to naturally tailor it to their individual needs. By monitoring what activities are undertaken in the school garden and in the classroom, there is an opportunity to explore how intervention elements might be associated with dietary change.

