### Process measures evaluation

The process measures questionnaire will explore the differences between schools with different levels of adherence to the intervention programmes. The process measures evaluation will also identify which schools have or have not improved their gardening curriculum from baseline to follow-up using regression analysis.

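### The efficacy subset is chosen on participation after randomisation, so its gap from ITT mixes selection with effect and cannot be read as a difference in effect size

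*Protocol article*

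**What the plan says.** The main principle is intention-to-treat: "Analysis will follow the principle of intention-to-treat as far as possible" (protocol article, Discontinuation criteria). The section Subgroup analyses then lists an efficacy subset analysis among items that "will be investigated in an exploratory manner using the same modelling procedure as above", and adds: "These will be tested at the 1% significance level". It justifies the subset by saying that "the degree to which schools participate in the intervention is vital to the main outcome", and states the purpose: to "compare the results from ITT and efficacy subset analysis to examine the differences in effect size generated".

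The model to be re-used is described under Primary analyses: "The single covariate for the intervention group will be included in the model". Research questions and Proposed outcome measures, however, both define effectiveness by intake at follow-up adjusted for baseline.

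On participation, Process measures says that "level of involvement in the twilight sessions for both trials one and two will be recorded", that the regional advisor records further detail in the intensive schools, and that schools shape the programme to their own needs. It also puts the RHS benchmarking questions (gardening level 1 to 5) to schools at baseline and follow-up. Trial 2 comparison schools receive no active RHS intervention during the trial.

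**The concern.** Randomisation makes the full arms comparable. It does not make the active part of one arm comparable with the other arm. How far a school takes part is settled after allocation, largely by the school, and schools that take part fully may already differ in food culture and intake. In Trial 2 the comparison schools have no RHS programme to take part in, so the selection has no counterpart there. In Trial 1 both arms take part, but in programmes of different content, so equal participation does not pick out equivalent schools.

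The plan goes beyond showing the subset: it says what the comparison with ITT is for. A subset estimate larger than ITT would be taken as the effect under good delivery, although the same pattern can arise when the programme does nothing. The exploratory label limits the weight of the result but does not remove the bias.

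**Working it through.** **Inputs from the document.** Vegetable SD 85 g and ICC 0.125 (Proposed sample size); 16 v 16 schools in Trial 2; 50 children per school, 75% followed up, so 37.5; significance level 1%.

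**Assumptions not in the document.** One portion is 80 g. The correlation rho between a school's participation and its underlying mean intake is 0.3 to 0.5. The subset keeps 12 or 8 of 16 intervention schools. The true effect is zero.

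**Check on the inputs.** The plan gives no figure for this analysis, so I checked the inputs on its vegetable sample size. With 80 g per portion, half a portion is 40 g. At two-sided 5% and 90% power, n = 2 × (1.960 + 1.282)² × 85² / 40² = 95 per group, and 95 × 6.6 (stated design effect) = 627, as stated. The stated design effect does not match the stated ICC (1 + 49 × 0.125 = 7.125). That is a separate matter; the check below uses the ICC directly.

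**Step 1: school-level spread.** Between-school SD = 85 × √0.125 = 30.05 g. Sampling SD of a school mean = 85 × √(0.875/37.5) = 12.98 g.

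**Step 2: unadjusted bias.** If the k most active of 16 schools are kept, expected bias = rho × 30.05 × c. Here c is the mean of the top k of 16 standard normal values: 0.40 for k = 12 and 0.76 for k = 8.
- rho 0.3, k = 12: 0.3 × 30.05 × 0.40 = 3.6 g
- rho 0.5, k = 12: 0.5 × 30.05 × 0.40 = 6.0 g
- rho 0.3, k = 8: 0.3 × 30.05 × 0.76 = 6.9 g
- rho 0.5, k = 8: 0.5 × 30.05 × 0.76 = 11.4 g

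In portions this is 3.6/80 = 0.045 to 11.4/80 = 0.14. At rho = 0 the bias is zero. Full ITT on the same simulated data averages about 0 g and rejects in about 1% of trials at the 1% level.

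**Step 3: with baseline adjustment.** The school's baseline mean (50 children) was added as a covariate, in 8,000 simulated trials per setting. When adherence tracks baseline intake, the correlation of school intake over time was set at 0.5 to 1. When it tracks later intake, the correlation was set at 0.5 to 0.8.

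| rho | schools kept | unadjusted bias | 1% test rejects (unadjusted) | adjusted, adherence tracks baseline | adjusted, adherence tracks later intake |
|---|---|---|---|---|---|
| 0.3 | 12 | 3.6 g | 1.3% | 0.3 to 0.5 g | 1.7 to 3.0 g |
| 0.5 | 12 | 6.0 g | 2.0% | 0.5 to 0.8 g | 2.7 to 4.9 g |
| 0.3 | 8 | 6.9 g | 1.8% | 0.5 to 1.0 g | 3.2 to 5.4 g |
| 0.5 | 8 | 11.4 g | 3.4% | 0.8 to 1.6 g | 5.3 to 9.1 g |

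If later intake is what adherence tracks and school intake is perfectly stable, the last column falls to the one before it.

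**Step 4: precision of the alternative.** SD of the unadjusted ITT difference = √[(30.05² + 12.98²) × 2/16] = 11.6 g. The instrumental-variable estimate divides ITT by the difference between arms in the share participating: 11.6/0.75 = 15 g if 12 of 16 take part, 11.6/0.5 = 23 g if 8 of 16 do. The subset contrast has an SD of about 12 to 14 g. The near-zero bias of the instrumental-variable estimate when there is no effect holds by construction and is not evidence that it performs well when there is one.

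**The case against.** The strongest reply is that the article twice calls for adjustment for baseline, and baseline intake is exactly what a selected set of schools would differ on. This stands in part. If adherence follows baseline intake, adjusting for the school mean removes most of the bias. If it follows the course of intake after baseline, a material part remains. Adjusting only for the child's own baseline would remove less. The section Primary analyses names a single covariate, so the article does not settle which model the subset would use.

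The analysis is also exploratory, held to 1% and shown beside ITT. That stands, and it limits the severity. The subset has no explicit definition in this condensed article. That participation defines it is read from the sentence that introduces it, and the missing cut-off is not itself held against the plan.

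A reader might infer several stronger points that the documents do not support:
- **That no common measure of activity exists across arms.** The benchmarking questions go to schools at baseline and follow-up. A common scale still would not cure the problem, because follow-up gardening level is itself affected by allocation.
- **That false-positive rates at the 5% level apply.** The plan tests these analyses at 1%.
- **That the process evaluation repeats the error.** Its aim to "explore the differences between schools with different levels of adherence to the intervention programmes" is descriptive and claims no causal effect.
- **That non-adherence in Trial 2 is certain to be one-sided.** Twilight sessions are open to teachers from other local schools and the online resources are free (Study interventions).

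**Conclusion.** The concern holds in limited form. The subset is selected on a post-randomisation variable and the plan reads its gap from ITT as a difference in effect size. That reading is not protected by randomisation in either trial, and in Trial 2 the selection is confined to one arm.

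The size is uncertain. With no true effect, the false vegetable effect is about 4 to 11 g unadjusted and near 0 to about 9 g with school baseline adjustment, against a 40 g target. The upper unadjusted value is 11.4/40, about 28% of the target, and should not be quoted as the expected bias: it needs rho of 0.5, half the schools dropped and no baseline adjustment. Rho and the share of schools kept are assumptions that the document cannot confirm.

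It would be wrong to conclude that the trials' main result is at risk. ITT remains the primary principle and its conclusions are unaffected.

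**What to change.** **Trial 2.** Keep all schools as randomised. Beside the baseline-adjusted ITT, report a school-level instrumental-variable (CACE) estimate, with randomised arm as instrument and recorded RHS participation as exposure. Define exposure as any participation or the number of sessions attended. A high threshold should not be used: schools below it still receive advice and resources, which breaks the exclusion assumption if the programme works. Record any attendance by comparison schools, and state the exclusion assumption, namely that allocation affects intake only through the recorded participation.

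**Trial 1.** Drop the causal reading of the subset.

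**Both trials.** If a subset result is shown, adjust it for baseline intake, label it a non-randomised association, and remove the statement that its gap from ITT shows a difference in effect size.

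**Cost.** A change of wording and one further model. Twilight attendance is already to be recorded; attendance by comparison schools is a small addition. The price is a wider interval (SD about 15 to 23 g, against 12 to 14 g for the subset, in the unadjusted example) and an assumption that has to be stated and defended.
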